### 7.4 Definition of Evaluable Subjects, On Study, and End of Study

Participants who enroll in the study will be “evaluable.” De-identified data from subjects who sign consent for screening will also be used for creation of the Consort Diagram – to show which individuals were excluded or did not sign consent vs. those who were enrolled. Data from subjects who withdraw from the study will still be considered evaluable.

### 7.5 Early Study Termination

This study can be terminated at any time for any reason by the PI-sponsor – the National Institutes on Drug Abuse. If this occurs, all subjects on study will be notified as soon as possible. Additional procedures and/or follow up should occur in accordance with Section 10.6, which describes procedures and process for prematurely withdrawn patients.

## 8 STUDY DRUG

### 8.1 Names, Classification, and Mechanism of Action

#### Varenicline Tartrate

Alternate names: Varenicline, Chantix

Type of Study drug class: smoking cessation medication

Mechanism of action: Acetylcholine-Nicotinic receptor partial agonist/antagonist

#### Bupropion Hydrochloride – sustained release

Alternate names: Bupropion SR, Zyban, Wellbutrin.

Type of Study drug class: Antidepressant, appetite suppressant, smoking cessation medication

Mechanism of action: inhibits reuptake of synaptic dopamine and norepinephrine.

#### Nicotine patch

Alternate names: Nicoderm, transdermal nicotine patch

Type of Study drug class: smoking cessation medication

Mechanism of action: Acetylcholine-Nicotinic receptor agonist

### 8.2 Packaging and Labeling

All medications will be labeled according to Investigational Chemotherapy Service (ICS) Standard Operating Procedures to include at least: drug name/strength, quantity, lot number, and expiration or retest date. Placebo medications will be provided in non-descript packaging, similarly to non-placebo medications.

### 8.3 Supply, Receipt, and Storage

Pfizer will provide Varenicline and placebo Varenicline; nicotine patches, bupropion and placebo bupropion will be provided by Central Compounding Pharmacy Incorporated. CVS brand clear adhesive bandages will be purchased to serve as placebo nicotine patches. For individuals who do not have an adhesive allergy, but instead have other forms of skin sensitivity such as discoloration, redness, tenderness (which can be related to the adhesive used in specific brands of patch), an alternate placebo or active patch will be purchased. This will provide an alternative for participants who express concerns about these types of issues but would like to continue using nicotine patch. ICS will be responsible for managing the receipt and storage of all pharmaceuticals and placebo medications.

### 8.4 Dispensing and Preparation

Pharmaceuticals will be prepared and dispensed according to ICS Standard Operating Procedures. Study staff will collect the participant's pharmaceuticals from the ICS once the participant has arrived at the clinic and dispense them during the Study Visit.

### 8.5 Compliance and Accountability

Participants will be asked to return un-used medications at each visit. There are 4 study assessment visits at which medication management (Unused Medication Count and Dispensing Medications) will occur: Enrollment visit, Medication Response Visit, 2-week post quit visit, 12-week post quit visit:

**Enrollment Visit:** Provide 3 weeks of Medications

**Medication Response Visit:** (2-weeks after Enrollment visit): Provide 4 weeks of Medications (through quit day and through 2-week post quit visit) Unused medication count)

**2-week post Quit Visit:** (4 weeks after Medication Visit): Provide 9 weeks of Medications (through 12-week post quit visit) (Unused medication count)

**12-week post quit visit:** (10 weeks after 2-week post quit visit) (Unused medication count)

During each Unused Medication Count, the participant will bring unused medications to the study assessment visit. The CTA will then count these medications and record the outcome for an assessment of medication adherence. This data will also be recorded at ICS. In addition, ICS will collect all used medication bottles.

### 8.6 Disposal and Destruction

ICS will be responsible for destruction of unused medications and will follow standard research pharmacy procedures for this.

## 9 SUBJECT ELIGIBILITY

Patients who consent to participate in the study will be screened for the following inclusion/exclusion criteria.

### 9.1 Inclusion Criteria (assessed by research staff and/or study medical provider)

1. Age 18 years or older
2. Actively smoking 5 or more cigarettes per day for at least one year
3. Have a median CO of at least 7 ppm (on carbon monoxide breath test)
4. Willing to set a quit date within 6 weeks
5. Willingness to take Varenicline OR nicotine patch (patient choice) and Bupropion
6. Access to a telephone

### 9.2 Exclusion Criteria (assessed by research staff and/or study medical provider)

1. 5 or above for women OR 6 or above for men on the Alcohol Use Disorders Identification Test (AUDIT-C) are considered a "positive" screen and will require additional clinician assessment to determine if an alcohol use disorder is present.
2. Illicit drug use within the last month
3. 3 or above on Patient Health Questionnaire (PHQ-2) Depression Scale or >0 in PHQ-9 question 9
4. Daily use of a second form of tobacco or nicotine or smoking a product other than combustible cigarettes (e.g. e-cigarettes, cigars, chewing tobacco, snuff, hemp)
5. Current use of a smoking cessation medication (e.g. nicotine replacement, Varenicline, Bupropion)

6. Report of pregnancy, attempting to get pregnant, or actively breast feeding or positive urine pregnancy test (only given to females with child bearing potential)

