### 3.4 Selection of Subjects

This study will recruit participants through Quit at Duke, also called the Duke Smoking Cessation Program (DSCP), the Duke Primary Care Research Consortium, and the Duke Center for Smoking Cessation (CSC). The DSCP is a growing multi-clinic tobacco use treatment program. The Duke CSC is a research center dedicated to researching novel

treatments to help smokers break their addiction to nicotine. Subjects for this study will be required to be current smokers, confirmed by self-report and carbon monoxide testing (CO over 7) who are at least 18 years of age. Subjects additionally must also be willing to set a Quit Day (day they intend to stop smoking) within the next six weeks and be willing to use two medications together – either Varenicline and Bupropion or Nicotine Patch and Bupropion depending on their choice of regimen. Subjects will be excluded if they are currently pregnant or breast feeding, test positive for drug or alcohol abuse psychometrically, use a secondary form of tobacco or nicotine, are already taking a tobacco use treatment medication, have a symptomatic mental or physical illness, or are unwilling to engage in pharmaceutical and behavioral treatments for tobacco use.

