### **10.7.3. Subject-Rated Standardized Measures**

A participant's alcohol use is assessed at Baseline using the AUDIT-C (Appendix 9). A score of 3 or higher (if female) or 4 or higher (if male) is considered a "positive" screen, and will require additional assessment from the study clinician to determine if the participant can be included in the study..

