## **Appendix 9: Alcohol Use Disorders Identification Test (AUDIT-C)(Bush, Kivlahan, McDonell, Fihn, & Bradley, 1998)**

The next questions are about your alcohol use.

1. How often do you have a drink containing alcohol?

0= Never

1= monthly or less

2= 2-4 times a month

3= 2-3 times a week

2. How many standard drinks containing alcohol do you have on a typical day?

0= 1 or 2

1= 3 or 4

2= 5 or 6

3= 7 to 9

4= 10 or more

3. How often do you have six or more drinks on one occasion?

0 = Never

1 = Less than monthly

2 = Monthly

3 = Weekly

4 = Daily or almost daily

4. Calculate: Add all scores of 3 question above together.

Then reference score to gender:

3 or higher for females = likely alcohol abuse or dependence

4 or higher for males = likely alcohol abuse or dependence

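### The AUDIT-C score that triggers a clinician's alcohol assessment is 5 (women) or 6 (men) in the exclusion criteria, but 3 or 4 in the assessment section and on the form

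*Protocol*

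**What the plan says.** Four places in the protocol bear on the alcohol screen.

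- **Section 9.2, exclusion criterion 1**, counts as positive a score of "5 or above for women OR 6 or above for men on the Alcohol Use Disorders Identification Test (AUDIT-C", and says that such a screen "will require additional clinician assessment to determine if an alcohol use disorder is present".
- **Section 10.7.3**, on the baseline measures, has different numbers: "A score of 3 or higher (if female) or 4 or higher (if male) is considered" positive, and such a screen "will require additional assessment from the study clinician to determine if the participant can be included in the study".
- **Appendix 9**, the form itself, ends with a scoring key: "3 or higher for females = likely alcohol abuse or dependence" and "4 or higher for males = likely alcohol abuse or dependence".
- **Section 3.4**, in the synopsis, lists among those to be excluded people who "test positive for drug or alcohol abuse psychometrically". It names no instrument, cut-off or clinician step.

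All four are current text, and none explains the difference.

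**The concern.** A screening threshold should give the same answer whoever applies it. Here two sections define a positive result on the same instrument with different numbers. The criteria in section 9.2 may be assessed by research staff rather than a medical provider, so the printed number decides whether a clinician looks at the person's drinking at all. Staff working from 9.2 would not refer some people for whom 10.7.3 requires an assessment.

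Two things are at stake. The first is the screening safeguard. Adaptive-arm non-responders receive bupropion (section 10.2), and section 5.2 names acute alcohol discontinuation as a contraindication because of seizure risk. The second is auditability. If a woman scoring 4 is enrolled without a clinician's assessment, a monitor cannot say whether that is a deviation, because the answer depends on the section consulted.

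**Working it through.** No sample size, power or alpha figure is involved, so the check is a comparison of the texts.

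**Step 1: is it the same measurement?** Section 10.1 lists the AUDIT-C among the baseline measures taken at the screening examination, and section 10.7.3 says alcohol use is assessed at baseline. Sections 9.2 and 10.7.3 therefore refer to the same administration of the same instrument.

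**Step 2: classify each score under each rule.**

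| Sex | Score | Section 9.2 | Section 10.7.3 | Appendix 9 key |
|---|---|---|---|---|
| Women | 0–2 | negative | negative | below cut-off |
| Women | 3–4 | **negative** | **positive** | at or above cut-off |
| Women | 5 or more | positive | positive | at or above cut-off |
| Men | 0–3 | negative | negative | below cut-off |
| Men | 4–5 | **negative** | **positive** | at or above cut-off |
| Men | 6 or more | positive | positive | at or above cut-off |

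Width of the disputed band: women 5 − 3 = 2 points; men 6 − 4 = 2 points.

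**Step 3: could these be two tiers?** A lower score for referral and a higher one for exclusion would be coherent. The text does not allow that reading: 9.2 and 10.7.3 each use their own number to define a positive screen, and each attaches the same action to it, namely further assessment by a clinician.

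**Step 4: compare the consequences.**

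| Place | What a positive screen leads to |
|---|---|
| 3.4 | exclusion, no clinician step mentioned |
| 9.2 | clinician assesses whether a disorder is present; what follows from that finding is not stated |
| 10.7.3 | clinician assesses whether the person can be included |
| Appendix 9 | a label only; no referral or eligibility rule |

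**Step 5: one case followed through.** A woman scoring 4 needs no referral under 9.2. Under 10.7.3 she needs a clinician's assessment. Under 3.4, read literally with the Appendix 9 key, she is excluded. At 5 or more for women and 6 or more for men the two operative sections agree, and only the synopsis differs.

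**The case against.** The best defence is that this is a mismatch in a referral trigger, not in eligibility. In both operative sections a positive screen leads to a clinician's assessment, so a woman scoring 3 or 4 could be enrolled under either. That stands. A reader might infer that eligibility itself flips with the section consulted; it changes only for people in the band whom a clinician would then keep out, and the documents do not say how many that would be.

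The defence also says that section 3.4 is a one-sentence synopsis. Read with the placing of the item under exclusion criteria, it may simply mean that a screen confirmed by the clinician leads to exclusion. That is a fair reading, and it makes the exclusion-versus-review difference secondary. It does not fill the gap in 9.2, which never states the outcome once a disorder is found. Appendix 9, likewise, is a scoring key that agrees with 10.7.3, not a third rule.

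On safety, a reader might infer that people below the 9.2 cut-off enter unguarded against the bupropion seizure risk. The documents do not support that. Section 9.3, criterion 10, excludes anyone currently discontinuing alcohol whatever the AUDIT-C score, and is assessed by the study medical provider. Criterion 7 excludes medical contraindications to the study drugs, Appendix 1 asks about acute alcohol discontinuation, and section 10 gives study medical staff access to the record. These safeguards reduce the consequence. They do not tell anyone which AUDIT-C score calls for the assessment.

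Finally, a reader might infer that the cut-off limits the AUDIT-C range in the predictor and moderator analyses. Neither 9.2 nor 10.7.3 excludes automatically on the score, so neither number truncates the range, and those analyses are exploratory.

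**Conclusion.** The contradiction in the cut-off is real, and no reading of the current text removes it. Its size is a band two points wide for each sex: women scoring 3–4 and men scoring 4–5 must be assessed by a clinician under 10.7.3 and need not be under 9.2. The differing consequence in 3.4 and the unstated outcome in 9.2 are secondary.

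No head count can be given. The protocol contains no expected AUDIT-C distribution and no number to be screened, and counting answer patterns on the form would not supply one, because the patterns are not equally likely.

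The effect is confined to who is referred and whether eligibility decisions can be audited; the sample size and primary analysis do not depend on it. The conclusion rests only on the wording of the four places cited. It should be fixed, but it does not threaten the trial's main result. Which cut-off is appropriate is for the investigators and is not judged here.

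**What to change.** The investigators should reconcile the passages to one pair of AUDIT-C cut-offs and one stated consequence of a positive screen, including what happens once a clinician finds an alcohol use disorder. The same numbers and the same consequence should then appear in sections 3.4, 9.2 and 10.7.3 and in the scoring key of Appendix 9. If enrolment has begun, the screening scores of women at 3–4 and men at 4–5 should be checked to see whether a clinician's assessment was recorded. The cost is an edit to the protocol and form, plus a short look-back where one is needed.

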### **9.3 Exclusion Criteria (assessed study medical provider)**

7. Medical contraindication to the use of Varenicline or Nicotine Patch, or Bupropion (including seizure disorder)
8. Brain abnormality that would increase the patients risk for a seizure (including but not limited to a stroke or brain tumor)
9. Bulimia or anorexia
10. Currently undergoing discontinuation of alcohol or sedative (including benzodiazepines, barbiturates, or antiepileptic drugs)
11. Use of MAO-inhibitor (currently or in the last 14 days)
12. Taking Linezolid or intravenous methylene blue.
13. Significant adverse reaction to bupropion in the past
14. Symptomatic cognitive or emotive disorder such as untreated schizophrenia, severe untreated depression, anxiety.
15. Uncontrolled hypertension (systolic BP >160 mm Hg, diastolic BP >100 mm Hg) or hypotension
16. Chest pain in the last month (unless history indicates a non-cardiac source) or myocardial infarction in the past year
17. Unstable irregular heart rhythm
18. Symptomatic cardiac disorder
19. Moderate renal impairment or mild hepatic impairment (study provider discretion)
20. Current symptomatic lung disorder/disease (including but not limited to COPD, emphysema, and asthma) that requires oxygen
21. Migraine headache occurring more than once per week
22. Unexplained fainting spell within the last month
23. Uncontrolled diabetes (blood sugars >200 more than once per week, suffering from complications or on insulin)
24. Current cancer or treatment of cancer in the past 6 months (except basal or squamous cell skin cancer)
25. History of Tuberculosis or positive PPD
26. Suicidal ideating within the past 12 months or attempted suicide within the last 10 years.
27. Psychiatric hospitalization in the past 12 months
28. Red dye allergy
29. Any other major medical conditions (study provider discretion)

## 10 TRIAL PROCEDURES AND ASSESSMENTS

### **Relationship of this study to the Duke Translational Smoking Cessation Program (TSCP) and Duke Center for Smoking Cessation (CSC)**

Study recruitment will take place among a clinical population via three routes - the TSCP Clinics, Duke Primary Care (DPC) Clinics, and the Center for Smoking Cessation (CSC).

**Duke Translational Smoking Cessation Program (TSCP):** Most patients in this study will be recruited through the Duke TSCP clinics – a network of six clinics throughout the Duke University Health System (DUHS) that receive roughly 250 patient referrals per month. The TSCP is a growing program expanding to serve patients across Duke Health. [name], the PI for this study, is Director of the TSCP and oversees all TSCP personnel and processes. Each TSCP Clinic site contains a provider trained in tobacco cessation treatment (typically an APP (Advanced Practice Provider)) who performs a thorough evaluation, conducts physical exams and prescribes medication and a Medical Assistant or Staff Assistant who assists with data collection. The TSCP is designed with a research infrastructure in which data is collected in a standardized format and research staff who recruit patients are present on site for studies. The TSCP contains centralized operations including a clinic coordinator who calls patients for scheduling and follow up. Every patient who is scheduled for an appointment at a clinic within the TSCP will be screened for research study eligibility. If a patient could potentially be eligible for a research study, a note will be made in their medical chart. Research staff will then attempt to reach out to them to see if they are interested in participating in a research study (via MyChart message and then via phone). If the patient is interested in the study and meets the inclusion criteria, the patient will be scheduled to meet research staff at the TSCP clinic or the CSC for a screening visit. If the potential participant is not interested in a research study or not eligible, a note will be made in their medical record and they will be encouraged to keep their regularly scheduled clinic visit.

**Duke Primary Care (DPC):** The study will also recruit participants through the Duke Primary Care (DPC) Clinics. Authorization has been provided by the DPC Research Consortium, which will provide access to smokers who have consented to be contacted for research. The Research Consortium manages multiple studies to avoid conflict between studies and will provide access to three DPC Clinics. DPC includes a network of 40 primary care clinics throughout Duke University Health System. Patients who attend visits with DPC medical providers at within Duke Primary Care are screened to see if they are willing to be contacted to find out about available research. DPC patients who are identified within the Electronic Health Record as being “current smokers” will be available for contact for our study. Using a regularly generated report, research staff will use participant MRN to look at their medical record to screen for eligibility (name, mailing address, email address, phone number, age, smoking history, allergies, emergency department visits for substance use, medications, and medical diagnoses). Ineligible participants will not be contacted. If eligible, research study staff will contact the eligible participant via phone and MyChart message to describe the study. MyChart messages will include information on opting out (center phone number). Any voicemails left will be non-descript and only including brief information that they may be eligible for a research study at Duke and a phone number to reach back out (no information provided on smoking status). If participants have previously opted-out of research (as noted in their medical record), they will not be contacted. If they are interested and meet inclusion criteria, the research staff will schedule them for a screening visit at the Duke Center for Smoking Cessation (CSC) (central study site).

**Other Research Studies:** Potential subjects will be recruited through pre-screen failures from other studies at the CSC. There are currently several studies recruiting smokers from communities in and around Durham, North Carolina through newspaper flyers, internet and TV advertisements, and word-of-mouth. If potential subjects fail to meet the pre-screening study requirements for these studies (Pro: 00074741, Pro: 00042277) at the CSC, but are still interested in research, they will be routed to a CTA to be pre-screened for this study over the phone. If potential subjects meet the pre-screening study requirements and are still interested in participation, they will attend a physical screening session at the Duke CSC, located at [name]. At the screening on-site visit, a CTA will meet with the patient in a private area of the CSC (consent room) and provide the patient with the Study Consent Form for review.

**Advertisements:** Subjects will be recruited through internet-based ads on free websites (for example, Craigslist). The ad will feature a phone number and contact email for potential participants and can be found in the Recruitment section. A physical copy of this ad may also be produced to be used as a flyer advertising the study in Durham and the surrounding areas.

**Consent:** Interested individuals will be provided with the Study Consent Form (CF), which provides a description of the study. The CTA will review the consent form with the potential participant, read key sections out loud, clarify terms as needed, and answer questions. Ability to read and understand English will be assessed at this time. If unable, the consent process will be discontinued. After reviewing the CF, if the interested individual is interested in participation in the study, they will be asked to sign consent in order to continue screening (completion of exclusion criteria and pregnancy testing). This will include assessment of data collected in EPIC specifically for the Duke Smoking Cessation Program Initial Clinic Visit. The study medical staff (PA or MD) will have access to the potential participant's EPIC record in order to review the Duke Smoking Cessation Program Initial Clinic visit for participant eligibility as well as other pertinent elements of the patient's medical record to ensure their safe inclusion in the study. Individuals who pass Inclusion/Exclusion Criteria will be required to take a urine pregnancy test if they are of child-bearing potential, as defined by the Duke IRB.

| SCHEDULE OF ACTIVITIES                                    |                        |                         |                                  |                               |                                                          |                               |                                     |
|------------------------------------------------------------------|------------------------|-------------------------|----------------------------------|-------------------------------|----------------------------------------------------------|-------------------------------|-------------------------------------|
|                                                                  | Screening Phase | Treatment Phase  |                                  |                               | End of Treatment                                  | Phone Follow up Period | End of Study                 |
|                                                                  | Screening Visit | Enrollment Visit | Medication Response Visit | 2-week post Quit Visit | 12-week Post Quit Visit (Discontinue Medications) | Calls 1-9              | 52-week post quit phone call |
| Assessments/Observations                                  |                        |                         |                                  |                               |                                                          |                               |                                     |
| Assessment in-person                                             | X                      | X                       | X                                | X                             | X                                                        |                               |                                     |
| Obtain Informed Consent                                          | X                      |                         |                                  |                               |                                                          |                               |                                     |
| Assessment of Inclusion/Exclusion Criteria. Urine pregnancy test | X                      |                         |                                  |                               |                                                          |                               |                                     |
| Vitals and CO breath test                                        | X                      | X                       | X                                | X                             | X                                                        |                               |                                     |
| Psychometric measures                                            | X                      |                         |                                  | X                             | X                                                        |                               |                                     |
| Dispense Medications                                             |                        | X                       | X                                | X                             |                                                          |                               |                                     |
| Assess Medications                                               |                        |                         | X                                | X                             | X                                                        |                               |                                     |
| Phone Call Assessments                                           | X                      | X                       | X                                | X                             | X                                                        | X                             | X                                   |
| Assess Adverse Events                                            |                        | X*                      | X                                | X                             | X                                                        | X                             | X                                   |
| Payment                                                          |                        | X                       | X                                | X                             | X                                                        |                               | X                                   |

\*The Adverse Events questionnaire will be administered at the Enrollment visit in order to obtain baseline data on a patient's symptoms to better understand if the development of any SE is related to study drugs.

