**Contraindications:** The major contraindicated for bupropion are individuals with seizure disorder as bupropion is known to lower the threshold for seizures. Those undergoing acute discontinuation of alcohol and sedatives such as benzodiazepines should also not be prescribed for the same reason of increased seizure risk. It is also contraindicated in individuals with a diagnosis of bulimia or anorexia nervosa (GlaxoSmithKline, 2014). Individuals using Wellbutrin should not be prescribed additional bupropion. Bupropion should also not be started in individuals who have been taking Monoamine Oxidase inhibitors (MAOI) in the previous 14 days. It should also be avoided in those with hepatic impairment, pregnant women and if <18 years old (GlaxoSmithKline, 2014).

**Common Side effects:** The most commonly reported adverse reactions of bupropion (incidence  $\geq 5\%$  and  $\geq 1\%$  more than placebo rate) are: sleep disturbances, dry mouth, rhinitis, dizziness, anxiety, nausea, constipation, and arthralgia (GlaxoSmithKline, 2014).

Insomnia: 30 - 40%

Dry mouth: 10%

Constipation, pruritis and pharyngitis: <10%

Approximately 7-12% of individuals who report these adverse effects discontinue using bupropion, although some studies have reported 31 - 33% of individuals on a 300mg dose of bupropion discontinuing medications due to side effects and 25% of those on 150mg discontinuing medication due to side effects (J. R. Hughes, Stead, Hartmann-Boyce, Cahill, & Lancaster, 2014; Richmond & Zwar, 2003). Allergic reactions such as pruritus, hives, angioedema and shortness of breath have been described at a rate of 1-3 per thousand (J. R. Hughes et al., 2014; Richmond & Zwar, 2003).

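### The time-dependent contraindications to bupropion are checked only at Screening, at least 21 days before the first dose, and are not actively re-asked when bupropion or its placebo is dispensed

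*Protocol*

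**What the plan says.** The Schedule of Activities in protocol section 10 has one eligibility row, "Assessment of Inclusion/Exclusion Criteria. Urine pregnancy test", marked under the Screening Visit and blank elsewhere.

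Section 5.2 (Bupropion, Contraindications) ties two conditions to the time the drug is given. On MAO inhibitors: "Bupropion should also not be started in individuals who have been taking Monoamine Oxidase inhibitors (MAOI) in the previous 14 days". On withdrawal: "Those undergoing acute discontinuation of alcohol and sedatives such as benzodiazepines should also not be prescribed for the same reason of increased seizure risk".

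Section 9.3 carries these into eligibility as exclusion 10 ("Currently undergoing discontinuation of alcohol or sedative (including benzodiazepines, barbiturates, or antiepileptic drugs") and exclusion 11 ("Use of MAO-inhibitor (currently or in the last 14 days"), and adds exclusion 12 ("Taking Linezolid or intravenous methylene blue"). The questions that would detect them are in Appendix 1, which section 10.7.1 treats as a baseline measure. AUDIT-C is also a baseline measure (section 10.7.3).

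Bupropion or placebo is chosen from the response seen two weeks before the quit day. Section 8.5 describes the supply at that Medication Response Visit as "2-weeks after Enrollment visit): Provide 4 weeks of Medications (through quit day and through 2-week post quit visit". Section 10.2 starts the pills one week before the quit day.

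**The concern.** Exclusions 10, 11 and 12 describe states that change over time, and section 5.2 makes the first two matter when bupropion is started or prescribed. The protocol asks about them once, before any study drug is given, and schedules no further question before bupropion is handed over. Someone eligible at Screening may afterwards begin an MAO inhibitor or linezolid, receive intravenous methylene blue, or begin withdrawing from alcohol or a sedative. If they do not volunteer this, staff who follow the Schedule as written can give them bupropion that the protocol says they should not have. For withdrawal, the stated reason is seizure risk. Contact staff do not know who will receive active drug (section 7.1.5), so they cannot direct the question at those who need it.

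**Working it through.** The protocol gives no figure to reproduce. The check is a timeline, with the target quit day as day 0.

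**Inputs**
- Enrollment and first pre-quit drug: day -28 (sections 8.5 and 10.2). Screening is on or before that day (section 10.1).
- Medication Response Visit: 14 days after Enrollment, so day -14 (section 8.5).
- First bupropion or placebo dose: day -7 (section 10.2). The next visit after day -14 is two weeks post-quit, so these pills must be dispensed on day -14.
- Pre-quit calls: one day after Enrollment, one day before the Medication Response Visit and one day before the quit day (section 10.4), so days -27, -15 and -1.

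**Check to first dose**
- As written: at least 28 - 7 = 21 days. If the six-week limit on setting a quit date (section 9.1) is assumed to run from Screening, at most 42 - 7 = 35 days.
- With a re-check on day -14: 14 - 7 = 7 days.

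**MAO-inhibitor window**
- The 14 days before a day -7 dose are days -21 to -8.
- Screening on its latest possible day, -28, looks back over days -42 to -29. Overlap with the window: 0 of 14 days.
- A re-check on day -14 looks back over days -28 to -15. Overlap: days -21 to -15, which is 7 of 14 days.
- The other 7 days (-14 to -8) fall after dispensing. No call is scheduled between days -14 and -7; the next is on day -1, six days after the first dose. An instruction at dispensing has to cover this week.

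**What is asked between Screening and the first dose**
- Section 10.7.6 lists medications as a phone topic, and one call falls on day -15. It refers to Appendix 19 for the questions. The Appendix 19 item used before quitting concerns side effects; its question about other drugs is for weeks 26 and 52 and covers cessation drugs only. The Appendix 11 phone items concern adherence to study drug.
- The Schedule's medication-assessment mark at the Medication Response Visit corresponds to the unused-pill count in sections 7.1.3 and 8.5.
- No printed question after Screening and before the first dose asks about non-study drugs or about stopping alcohol or a sedative.

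**Who could receive active bupropion**
Only non-responders in the adaptive arms. At the 50% in section 3.2: 0.50 × 150 = 75. At the non-responder rates in the sample size section: 0.588 × 75 + 0.646 × 75 = 44.1 + 48.5, or about 93. This is the number given the drug, not the number with a new contraindication, which the protocol does not give.

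**The case against.** The strongest reply is that the protocol is not silent. Section 7.1.4 has participants stay on their current medications, which argues against stopping a prescribed sedative, and asks them to report new ones. A negative Screening means that any later MAO-inhibitor or linezolid exposure is a new start, so reporting would catch it. A positive AUDIT-C "will require additional clinician assessment to determine if an alcohol use disorder is present". Medications are a phone topic the day before dispensing. Side-effect reports go to a physician or physician assistant, who may adjust dosing, and the investigator may withdraw anyone (sections 7.1.1, 7.1.2, 10.6.1). The adverse-event questionnaire and the consent form are not shown and may ask or say more. Exclusions 10 to 12 agree with section 5.2, so nothing is misstated.

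Much of this stands. A reader might infer that participants are unprotected after Screening; the documents do not support that. The safeguards are, however, passive (reporting), reactive (side effects) or discretionary (withdrawal). None is scheduled as a question before dispensing, and none says bupropion is held after a positive answer. Continuing current medications does not check whether a participant did so and does not address alcohol. Exclusion 10 covers only people withdrawing at Screening, so a later withdrawal is outside it.

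It is also fair that a day -14 re-check covers only half of the MAO-inhibitor window and that the rest again relies on the participant. That is a limit of the remedy; 7 of 14 days asked about directly is still better than none.

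**Conclusion.** The point holds as a low-severity patient-safety improvement. Under section 10.2 the only eligibility check is at least 21 days before the first bupropion dose. It covers none of the 14 days that section 5.2 makes relevant to MAO inhibitors, and it cannot detect later withdrawal or later linezolid or methylene blue use. This rests on Enrollment at day -28 and on the printed questionnaires being the questions actually used.

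Several stronger readings are not supported:
- **Effect on the trial result.** None is shown. Events are probably rare and their frequency is not given.
- **A day -14 bupropion start.** One sentence in section 3.2 adds bupropion two weeks before the quit day, but sections 3.3, 7.2 and 10.2 all use one week. The conclusion does not depend on it: that start would still come at least 28 - 14 = 14 days after the check.
- **Re-checking pregnancy or seizure disorder at the same visit.** The case here concerns exclusions 10 to 12 and does not establish a need for these items.
- **A missing intent-to-treat rule for withheld doses.** Sections 7.4, 10.6.3 and 13.4 already keep such participants in the analysis.

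**What to change.** Add one mark to the Schedule of Activities: a re-check of exclusions 10, 11 and 12 at the Medication Response Visit, before bupropion or placebo is dispensed. Use the three existing Appendix 1 questions (acute discontinuation; linezolid or methylene blue; MAO inhibitor in the past 14 days). Ask every participant, so that the question reveals nothing about allocation.

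Refer a positive answer to the blinded study medical provider. State that bupropion/placebo is withheld if the contraindication is confirmed and that the participant stays in follow-up.

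Because dosing starts 7 days later, tell every participant at dispensing not to start those pills, and to call the study, if any of these conditions arises in that week. The consent form may already say part of this.

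Cost: a few minutes at one visit, short additions to the protocol text, and a few withheld doses.
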